## Abstract

Geriatric assessment (GA) is fundamental to optimising cancer care in older adults, yet implementing comprehensive GA tools in real-world clinical settings remains a challenge. This study aims to assess the feasibility and acceptability of integrating information from patient-derived photographs (PhotoVoice) into enhanced supportive care (ESC) for older adults with cancer. A feasibility randomised controlled trial will be conducted at a regional cancer care centre in Australia. Participants aged 70 and above will be randomised into two groups: PhotoVoice plus ESC or usual care (ESC) alone. In the PhotoVoice group, participants will provide four photographs for deduction of representations of different aspects of their lives using photo-elicitation techniques. ESC will be conducted for both groups, incorporating PhotoVoice analysis in the intervention group. PhotoVoice may improve patient-centred care outcomes, including enhanced communication, shared decision making, and identification of patient priorities and barriers. Findings will provide insights into implementing PhotoVoice in geriatric assessment and guide future trials in cancer among older adults.

## 1. Background

Age is a significant risk factor for cancer, and the ageing process plays a crucial role in cancer progression and care. Older individuals aged 65 years and above account for a substantial proportion of cancer diagnoses and deaths [1,2]. Consequently, frail older adults are more susceptible to complications, treatment toxicity, increased hospitalisation, and mortality [3,4].

The ageing process is complex and heterogeneous, necessitating treatment decisions that go beyond chronological age and consider various biopsychosocial factors. These factors include comorbidities, geriatric syndromes, functional status, nutritional health, and socioeconomic characteristics [5,6,7]. Therefore, it is crucial to incorporate geriatric assessment (GA)-guided interventions, which consider frailty, comorbidity, and psychosocial domains, into the cancer care of older adults [5,8].

To improve the quality of care and address age-related concerns, multidimensional assessment of older adults with cancer has been shown to be beneficial. This approach enables personalised, patient-centred supportive care [1,2]. However, the implementation of such assessments is often suboptimal, particularly in regional and rural centres that encounter challenges such as a shortage of skilled healthcare professionals. This issue is particularly important when considering the critical role of a multidisciplinary team (MDT) in providing holistic cancer care. The integration of all professionals involved in the treatment decision-making process for older people with cancer enhances patient-centred supportive care during diagnosis, treatment, and follow-up periods, as well as palliative and end-of-life care management, and it is appreciated by most patients [5]. The objective of the MDT is to provide comprehensive, high-quality care that is congruent with the patient’s goals [9] identified through GA. Evidence from randomised control trials suggests that geriatric assessment guided interventions improve quality of life, decrease treatment-related toxicity, and reduce healthcare utilisation in older adults with cancer [10,11].

In geriatric oncology, MDT is defined as the collaboration between professionals from different specialised fields of practice who work together with the goal of enhancing patient care and treatment efficacy whilst minimising toxicity [5]. Geriatric oncology MDTs are usually made up of medical oncologists, geriatricians, oncology nurses, social workers, pharmacists, palliative care specialists, primary care physicians, nutritionists/dietitians, occupational therapists, physical therapists [3,9], psychologists, speech pathologists, nursing teams [12], and pastoral care [13].

Best practice guidelines for cancer care in older adults emphasise the importance of GA as a foundation for shared treatment decision making. The International Society of Geriatric Oncology (SIOG) recommend implementing GA for shared treatment decision-making in older adults with cancer [14,15]. The National Comprehensive Cancer Network (NCCN) guidelines highlighted 28 risk factors, including geriatric syndromes, comorbidities, and socioeconomic issues, that impact treatment outcomes and require assessment before recommending anticancer therapy [16]. The foundation of geriatric medicine lies in the utilisation of multidimensional GA, which is then followed by GA-informed intervention recommendations [17,18]. These recommendations are incorporated into patient-centred care plans, accompanied by ongoing follow-up.

The integration of geriatricians into MDTs and the routine use of GA in oncology practice have enhanced the care of older cancer patients [12,18]. Older adults who perform poorly on the GA have adverse outcomes after undergoing surgery including increased risk of post-operative mortality [7]. GA has been shown to have multiple benefits, including predicting treatment-related toxicities; assessing frailty accurately; guiding shared decision making; and informing non-oncologic interventions such as social support, polypharmacy management, nutrition interventions, physiotherapy, and psychological care [3,16]. These non-oncological interventions have been shown to enhance patient adherence, treatment tolerance, and improve quality of life [5].

Despite growing recognition of the importance of GA in guiding geriatric oncological treatment decisions, implementation remains limited. Only 36% of surgical oncologists collaborate with geriatricians, and 48% consider GA essential for decision making [19]. Time constraints and performance targets driven practice and MDTs that focus primarily on cancer pathology and treatment may neglect essential patient-centred information, leading to overtreatment and poor outcomes [3,20]. As such, there is a need to explore innovative methods to streamline assessment information gathering. 

PhotoVoice is a qualitative research method that utilises photography and storytelling [21,22]. In cancer care, PhotoVoice could be used to explore the patient’s experience and perception of cancer. It may enhance clinicians’ understanding of older patients’ lived experiences, empower patients, and increase self-awareness [21]. By capturing the strengths and challenges of an older adult’s environment, PhotoVoice may optimise person-centred care [23]. It enables patients to take the lead in discussions, providing richer descriptions and addressing important topics [22] that may be missed during busy routine practice. Moreover, PhotoVoice promotes patients’ awareness of the factors influencing their health and treatment decisions [24]. In conventional photovoice, participants typically receive a camera to capture photos for later discussion [23]. In our proposed study, participants will provide photographs they select from their existing collection.

Our proposed study will investigate the utility of integrating PhotoVoice discussion of patient-supplied photographs into GA-guided ESC and examine its potential to contribute to patient-centred care. Enhanced Supportive Care refers to a comprehensive approach that engenders addressing the physical, emotional, social, and practical needs of patients with cancer [25,26]. It involves providing additional interventions, services, and resources to optimise the overall well-being and quality of life of patients throughout their cancer journey [25].

Implementation of PhotoVoice in our study is undergirded by the Bronfenbrenner model [27]. The model is based on the theory that understanding individuals and their behaviours is underpinned by the reciprocal interaction between individuals and their environment. Its domains include the individual, microsystem (immediate relationships), mesosystem (connections between microsystems), exosystem (indirect influences), and macrosystem (broader cultural factors), representing the multidimensional nature of development and its interconnected influences [27].

The study objective is to investigate the feasibility and acceptability of implementing PhotoVoice in addition to usual care in a regional cancer centre. Usual care in this context is defined as ESC that incorporates geriatric assessment. Given the early stages of ESC, a secondary aim is to undertake a quality improvement exercise to examine aspects of ESC adoption using a medical records audit. The primary and secondary research questions are, respectively, (i) what is the feasibility, acceptability, and utility of PhotoVoice to enable empowerment, patient-centred care, and shared decision making for older adults diagnosed with a cancer in a regional cancer centre? and (ii) using a medical records audit, what is the level of uptake of supportive (non-medical) care practice as demonstrated by a range of tools as proxies for supportive care including use of the distress thermometer (DT), electronic rapid fitness assessment (eRFA) and referrals to supportive care services before and during the implementation of PhotoVoice?

## 2. Methods

### 2.1. Study Design

The study will be a feasibility and acceptability randomised controlled trial comparing PhotoVoice-augmented ESC with usual care in a regional geriatric oncology service (Figure 1). The RCT will be supplemented with a pre and post clinical quality improvement audit to evaluate GA use in the cancer centre.

### 2.2. Population and Setting

This study will involve older adults aged 70 years and above who have been diagnosed with a new cancer and referred to Border Medical Oncology and Haematology (BMOH) at the Albury Wodonga Regional Cancer Centre (AWRCC). This specialised cancer centre is located on the border between New South Wales and Victoria in regional Australia. BMOH provides care to a population of patients with cancer, including an annual intake of nearly 800 individuals aged over 69 years. The most frequently observed tumour types at BMOH include breast, prostate, colorectal, lung cancer, and melanoma.

## 3. Procedure

### 3.1. Screening

Prior to obtaining consent and randomisation, potential participants will undergo routine screening using the simple but sensitive G8 tool designed for assessing frailty among elderly patients who have been diagnosed with cancer [17]. The G8 is a validated geriatric screening tool consisting of eight items, which is based on the Mini Nutritional Assessment [28]. It has been validated and used in older patients with cancer [17,29]. Patients who score ≤14 on the G8 are considered vulnerable and therefore more likely to benefit from a comprehensive geriatric assessment [6], thus being eligible for the study. Eligible patients will be randomised to PhotoVoice plus usual care or usual care alone.

### 3.2. Inclusion and Exclusion Criteria

Prospective participants aged ≥70 years, with a diagnosis of cancer and newly referred for treatment at the AWRCC, scoring ≤14 on the self-reported G8 tool, and providing informed consent (including via an authorised proxy) will be included. Patients receiving treatment as an in-patient in the AWRCC will be excluded.

### 3.3. Randomisation

Participants will be randomly assigned to either PhotoVoice and ESC (Intervention) group or ESC only (Control) using a 1:1 computer-generated randomisation schedule created by an independent researcher. Allocation numbers will be placed in sealed opaque envelopes and drawn sequentially for each eligible participant.

### 3.4. Intervention (PhotoVoice Optimised ESC)

The intervention follows the usual care process described below, with the addition of PhotoVoice as a strategy to enhance the collection of patient-centred information. Participants will be asked to provide four photographs based on the following themes informed by the Bronfenbrenner model [27]:A photograph depicting an aspect of their identity, career, workplace, or life role, emphasising their personal journey.A photograph representing something important to the patient, such as a pet or family member.A photograph showcasing the patient’s home environment.A photograph illustrating their means of transportation to appointments.

These photographs will be discussed using established PhotoVoice photo-elicitation techniques based on the Modified SHOWeD questions [30]. The questions will guide the discussion, exploring the meaning and relevance of the images to the patient’s life and care. They may focus on identifying strengths, problems, and potential actions for patient-centred care.

The MDT will review the findings from the assessments and incorporate the analysis of the PhotoVoice images. This combined information will inform the care decision-making discussion and development of a management plan that aligns with the patient’s priorities. Depending on the identified deficits, impairments, and the patient’s preferences and strengths as gleaned from the PhotoVoice and MDT discussions, referrals may be made to services such as allied health, social supports, and assistive equipment services, etc.

### 3.5. Usual Care (ESC)

The care pathway includes screening and assessment tools including the G8 [17], the mood disorders screening DT [31], eRFA [32], body mass index (BMI) measurement, the Timed Up and Go (TUG) [33], and the Mini-COG for cognitive impairment screening [34]. The eRFA is a multidimensional electronic geriatric assessment questionnaire that takes around 15 min to complete on a tablet or computer [32]. The TUG test is a widely used tool for the assessment of a patient’s mobility, balance, and transfer abilities, thus assessing limitations in their functional activities [33]. At the initial consultation, patients undergo these assessments with the supervision of a cancer care nurse coordinator (G8 and DT). Patients scoring ≤14 on the G8 complete the eRFA on a tablet device, in addition to the TUG and Mini-COG.

The results are evaluated by the geriatric oncology MDT during their weekly meeting, which consists of various healthcare professionals. Based on this evaluation, personalised supportive care recommendations are made. The treating oncologist utilises the MDT’s evaluation report to inform treatment and care decisions.

### 3.6. Recruitment

After obtaining ethical approval, all patients presenting for their first appointment with any of the medical oncologists or haematologists during the period from February 2021 to January 2022 with a G8 score ≤14 would be offered enrolment in the study. The attending medical oncologist or haematologist would provide the patient with a participant information and consent document. Patients expressing interest in the study would be referred to the research team member (for a detailed study briefing), followed by obtaining informed consent. Prospective participants requiring more time to decide on participation would be given up to two business days to consider before following up if they had not responded.

All members of the MDT will receive a study briefing and invitation to participate during their weekly team meeting. They will be asked to complete a clinician survey (Appendix A), and consent will be implied by returning a completed survey.

### 3.7. Data Collection and Analysis

Demographic and characteristic data, including age, gender, cancer diagnosis, and comorbidities, will be collected from participants who provide a signed consent. Participant characteristics will be summarised using descriptive statistics, such as means and standard deviations for continuous variables, median and interquartile ranges for ordinal variables, and percentages for categorical variables.

Once the photographs have been collected within the next 1–2 scheduled appointments with the oncologist, a researcher will conduct a telephone or Zoom interview (Appendix B) with the patient, using PhotoVoice photo elicitation techniques to explore their priorities, barriers, and supports. The audio recorded interview will be transcribed verbatim and followed by thematic analysis. Themes will be guided by and grouped into the Bronfenbrenner model domains [27] to understand the older adult diagnosed with cancer as an individual in and how they influence and are influenced their social environment. A summary case report presenting the photographs along with a brief interpretation of their implications and salient aspects will be generated for the MDT meeting timed to occur before scheduled oncology appointments 2–3. As authorised proxies will be permitted to provide consent for participation, they will also be allowed to assist or provide responses on behalf of participating patients.

For participants in the usual care group, data collection will include a management plan based on the patient’s priorities determined through the usual care process.

In addition, surveys will be administered to both participating patients (Appendix C) and clinicians involved in the study (Appendix A). The tools used for the surveys will include the Health Care Climate Questionnaire [10,35,36,37], Perceived Efficacy in Patient-Physician Interactions Scale [10,38], Control Preferences Scale [10,39], and Treatment Decision-Making Form [10].

The implementation and impact of ESC on patient communication regarding age-related concerns will be compared before and after the first visit. Patient-centred care and shared decision-making outcomes between the PhotoVoice plus ESC and ESC only will be compared. Follow-up outcome data collection will be timed to take place 4–8 weeks after the MDT meeting.

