## Appendix C. Patient Survey

Health Care Climate Questionnaire and Health Care Climate Questionnaire Modified for Aging-Related Concerns

**Satisfaction with Overall Communication about Overall Health**	**Strongly Agree**	**Agree**	**Neutral**	**Disagree**	**Strongly Disagree**
1. Your cancer doctor encouraged you to **ask questions**.					
2. Your cancer doctor was **willing to discuss** any topic of importance to you.					
3. Your cancer doctor **gave you information** you could understand.					
4. Your cancer doctor helped you to **feel comfortable** discussing what to expect in the future.					
5. You feel **understood** by your cancer doctor.					

**Satisfaction with Communication about Other Medical Issues and Aging Concerns**	**Strongly Agree**	**Agree**	**Neutral**	**Disagree**	**Strongly Disagree**
1. Your cancer doctor encouraged you to **ask questions** about your other medical issues in addition to the cancer and/or any health concerns that could be from aging.					
2. Your cancer doctor was **willing to discuss** your other medical issues in addition to the cancer and/or any health concerns that could be from aging.					
3. Your cancer doctor **gave you information** you could understand about your other medical issues in addition to the cancer and/or any health concerns that could be from aging.					
4. Your cancer doctor helped you to **feel** **comfortable** discussing how cancer treatment could affect your other medical issues in addition to the cancer and/or any health concerns that could be from aging.					
5. You feel your cancer doctor **understood your overall health**, including your other medical issues in addition to the cancer and/or any health concerns that could be from aging.					
6. I understand why my cancer doctor suggested my treatment plan because he/she **talked with me about my medical tests** and procedures and how it led to my current diagnosis.					
7. You feel your cancer doctor **understood you** as a person, including values and beliefs important to you.					

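### The before/after-first-visit comparison of communication is, on its natural reading, not achievable as written, and on any reading cannot support a statement about the impact of ESC

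*Protocol article*

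**What the plan says.** Section 3.7 (Data Collection and Analysis) names two patient-level comparisons. The first is within patients: "The implementation and impact of ESC on patient communication regarding age-related concerns will be compared before and after the first visit". The second is between the arms, on patient-centred care and shared decision making. The section dates follow-up outcome collection at 4–8 weeks after the MDT meeting.

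Section 3.6 (Recruitment) offers enrolment to "all patients presenting for their first appointment with any of the medical oncologists or haematologists" who score 14 or less on the G8. It then sets the order of events: "The attending medical oncologist or haematologist would provide the patient with a participant information and consent document". Next: "Patients expressing interest in the study would be referred to the research team member (for a detailed study briefing), followed by obtaining informed consent". Those who need longer "would be given up to two business days to consider". Section 3.2 restricts entry to patients "newly referred for treatment at the AWRCC".

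The patient survey in Appendix C has two blocks, one headed "Satisfaction with Overall Communication about Overall Health" and one on other medical issues and ageing concerns. Both ask the patient to rate their cancer doctor.

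On exposure to ESC, the Abstract states: "ESC will be conducted for both groups, incorporating PhotoVoice analysis in the intervention group".

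**The concern.** A before/after comparison needs a before value that can be collected and that measures the same thing as the after value. The recruitment sequence and the questionnaire wording both appear to rule this out if the first visit is the first appointment. The sentence also attributes the change to ESC, although every participant receives ESC.

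The risk is that a before score is improvised, for example by handing out the survey in the waiting room or by asking patients to recall. A rise in the score could then be reported as a benefit of ESC when it reflects no more than having met the doctor.

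**Working it through.** No arithmetic applies. The check sets the stated sequence, the instrument and the exposure by arm side by side.

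**1. Sequence of events (protocol article, sections 3.1 and 3.3 to 3.7)**

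| Step | Event | Source |
|---|---|---|
| 1 | First appointment: G8 and DT; the attending doctor gives the consent document | 3.5, 3.6 |
| 2 | Research briefing, then consent; up to two business days to decide if needed | 3.6 |
| 3 | Randomisation by sealed envelope | 3.1, 3.3 |
| 4 | PhotoVoice arm only: photographs over the next 1–2 appointments, then interview | 3.7 |
| 5 | MDT meeting; its report goes to the treating oncologist | 3.5, 3.7 |
| 6 | Follow-up outcomes, 4–8 weeks after the MDT meeting | 3.7 |

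Consent (step 2) follows contact with the doctor (step 1). Under this process the number of participants with consented survey data from before the first appointment is zero. Routine G8 screening does precede consent, but it measures frailty, not communication. The patient survey is not listed among the routine assessments in section 3.5.

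**2. Instrument (Appendix C)**

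The outcome named in section 3.7 is communication about age-related concerns. This corresponds to the second block of Appendix C, the Health Care Climate Questionnaire modified for ageing. Its items ask whether the doctor encouraged questions, was willing to discuss, gave information and understood the patient. All of them refer to an encounter that has already taken place. A newly referred patient has no such encounter to rate before the first appointment.

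**3. Exposure to ESC**

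| Arm | ESC | PhotoVoice |
|---|---|---|
| Intervention | Yes | Yes |
| Control | Yes | No |

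Neither of the two arms is without ESC, so randomisation identifies the effect of adding PhotoVoice and not the effect of ESC. A within-patient change has no concurrent control. Across the first appointment it cannot be separated from first contact with the doctor.

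**4. Timing of ESC**

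ESC assessments start at the initial consultation (section 3.5), but the MDT evaluation reaches the oncologist afterwards, as a report. A score taken soon after the first appointment would precede the part of ESC most able to change how the doctor communicates.

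**5. Other sources of an ESC contrast**

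The records audit compares ESC use before and during the trial. Its checklist (Appendix D) records tools and referrals, not patient-rated communication, so it cannot supply the missing comparison.

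**The case against.** The strongest reply is that first visit is undefined. The article also speaks of a first appointment, an initial consultation and appointments 2–3. If a study visit or the first visit after the MDT meeting is meant, a post-consent before score is possible. This stands as a limit on certainty, so a flat statement that the comparison is impossible would go too far. Nothing in the text points to the later reading, however, and it would leave the change uncontrolled.

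A second reply is that the sentence in section 3.7 names no instrument. Two of the other listed scales, on perceived efficacy in patient-physician interactions and on control preferences, are not reproduced, so whether they can be answered before meeting the doctor cannot be checked. This also stands, although the named outcome matches the ageing-concerns block closely.

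A reader might draw three stronger conclusions that the article does not support:

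- **That there is no contrast for ESC at all.** A before/after change is a contrast in form. Its fault is that it is uncontrolled and confounded.
- **That the trial has no usable baseline.** The article does not exclude a baseline survey, and exact survey times may be in the fuller protocol.
- **That the comparison of PhotoVoice plus ESC with ESC is damaged.** It is a separate sentence in section 3.7 and is unaffected.

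**Conclusion.** The point holds in a limited form. On the natural reading of first visit, section 3.7 conflicts with section 3.6 and Appendix C: no consented before score exists, and a score obtained anyway would rate a doctor not yet met. On any reading, the within-patient change cannot carry a statement on the impact of ESC, because both arms receive ESC and no concurrent group without it is observed.

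This rests on three assumptions: that first visit means the first oncology or haematology appointment, that the outcome is the ageing-concerns block of Appendix C, and that the survey is not given as routine care before that appointment. The conclusion about ESC impact needs none of them.

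The defect has no numerical size beyond these counts. The documents give no correlation between baseline and follow-up scores, so no gain in precision from the repair can be quantified.

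This should be fixed, but it does not threaten the trial's main purpose. The first research question concerns the feasibility, acceptability and utility of PhotoVoice, the second concerns ESC uptake by audit, and neither depends on this sentence.

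**What to change.** 1. Delete the before/after comparison and its reference to the impact of ESC. Alternatively, define the visit, confirm that consent precedes the before measurement, and restate the change as descriptive with no causal claim.
2. Fix the first patient survey after consent, and hence after the first appointment, and before the allocation envelope is opened. Patients can then rate a doctor whom they have met, and their answers cannot be influenced by allocation.
3. Compare PhotoVoice plus ESC with ESC on the communication score at the 4–8 week follow-up, adjusted for that baseline, and report the difference as an estimate with a 95% confidence interval.

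Step 1 is the minimum repair. Steps 2 and 3 replace the lost comparison with one that the randomisation supports. The cost is a wording change, one fixed survey time and one short questionnaire per consenting patient.
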